### Trial design {8}

The study design is a randomized, double-blind, controlled clinical superiority trial. Participants will be randomized into three groups in a 1:1:1 allocation ratio: (1) the intervention group (LIPUS stimulus), (2) the control group (null stimulus), or (3) the self-control group (stimulated vs non-stimulated areas). Treatment is expected to last 7 days, and participant recruitment and data collection will be completed within 12 months. The study protocol flow chart is described in Fig. 1.

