### Intervention description {11a}

All participants will participate in a health education of approximately 20 min led by the research assistant prior to intervention treatment. The content of the education includes the transmission route of viruses, preventive measures, clinical manifestations, general treatment measures, etc. It is recommended that patients maintain hygiene, exercise moderately, drink an appropriate amount of water, and have a light diet.

Participants in the intervention group will be treated with wearable LIPUS therapeutic apparatus (UT – HP 05 21, Shanghai, China) for 7 days at a frequency of 572 kHz, an intensity of 820 mW/cm^2^, and a duty cycle of 50% (1 s inter-stimulus interval). The apparatus consists of two movable ultrasound probes and a central device. The operator fixed the ultrasound probes on the patient’s chest or back and adjusted the position of the probes according to the shape and scope of the lung lesion to perform vertical or parallel sonication therapy (Supplementary Fig. 1). During hospitalization, patients received 30-min treatments at 8:00 am and 2:00 pm daily.

Participants in the control group will be given a “null stimulus,” that is, the LIPUS therapeutic apparatus will be worn but the sonication treatment will not be started. These patients will be treated at the same time of day as the patients in the test group, but neither the patients nor the operators of the LIPUS equipment are aware of the grouping.

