Participants in the self-control group will be compared the LIPUS-treated area with the non-treated area in the lungs. First, a CT examination is performed to locate the body surface of the inflammatory exudative area. If the patient has bilateral pulmonary exudative inflammation, LIPUS treatment will be performed on one side of the lung, and the other will serve as the self-control group. Limited by the frequency of LIPUS, ultrasound cannot penetrate through one lung tissue to the other, and its maximum penetration depth is limited to the inside of the target lung. If the patient has unilateral pulmonary exudative inflammation, the inflammatory area will be divided into the upper and lower areas, and a single-area stimulus will be performed. The diameter of the two ultrasound probes is approximately equal to the width of the intercostal space, and the probes can be placed in the same intercostal space or in different intercostal spaces. The direction of sound beam can be adjusted manually. Limited by the width of the sound beam and the plane of sonication, the non-target inflammatory area above or below can be considered not to be affected.

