### Implementation {16c}

The sealed envelopes will be opened and reconcealed during the first LIPUS stage, before intervention by the staff responsible for randomization. The code will then be notified to the LIPUS experimenter.

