## Assignment of interventions: blinding

### Who will be blinded {17a}

Both patients and clinic staffs (caregivers, outcome assessors, and statistical analysts, etc.) will remain blind to group allocation. Whether the intervention is LIPUS-treated or non-stimulated will not be revealed throughout the study.

The clinician ([name]) who performed LIPUS therapy was not blinded to the grouping results and the course of treatment. The clinicians, [name] and [name], have access to the final trial dataset.

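### Operator blinding is stated in two opposite ways, and no rule assigns the treated area in the self-control group, so that within-patient contrast is open to selection

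*Protocol article*

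**What the plan says.** All places are in the protocol article.

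- **Trial design {8}:** "The study design is a randomized, double-blind, controlled clinical superiority trial".
- **Intervention description {11a}, control group:** "the LIPUS therapeutic apparatus will be worn but the sonication treatment will not be started". It adds, of these sessions, "but neither the patients nor the operators of the LIPUS equipment are aware of the grouping". For the active device, the operator "adjusted the position of the probes according to the shape and scope of the lung lesion".
- **Intervention description {11a}, self-control group:** with disease in both lungs, "LIPUS treatment will be performed on one side of the lung, and the other will serve as the self-control group". With disease in one lung, the inflamed region is split into an upper and a lower part and one part is stimulated. Neither sentence says how the side or part is picked.
- **Sequence generation {16a} and concealment {16b}:** patients are randomised 1:1:1 to three groups. No second randomisation is described.
- **Implementation {16c}:** "The sealed envelopes will be opened and reconcealed during the first LIPUS stage, before intervention by the staff responsible for randomization". Then: "The code will then be notified to the LIPUS experimenter".
- **Who will be blinded {17a}:** patients, caregivers, outcome assessors and analysts are blind, but the clinician "who performed LIPUS therapy was not blinded to the grouping results and the course of treatment".
- **Primary outcome {12}:** two comparisons are named, test group against control group, and treated against non-treated areas within the self-control group. An expert chest radiologist assesses the CT images, and area and volume absorption rates (AAR, VAR) are calculated for the target site.

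**The concern.** There are two linked problems. First, the article both asserts and denies that the person applying LIPUS is blind. A reader who meets only the Trial design and Intervention description sections would credit the trial with a safeguard that it does not have.

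Second, the self-control group is meant to remove differences between individuals. It removes differences between patients, but not differences between the two areas of one patient. Those are balanced only if the treated area is assigned by chance or by a rule unrelated to prognosis. If an informed operator picks the larger, denser or more recent lesion, the two areas may be expected to change by different amounts with no ultrasound effect at all. The result would then enter a comparison that the protocol counts as primary, and the Discussion also uses the self-control group to decide how the trial's result is to be read.

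**Working it through.** **Step 1. Blinding statements side by side.** {11a} says equipment operators are unaware of the grouping. {16c} says the experimenter is given the code after an envelope opening that precedes intervention. {17a} says the treating clinician is not blind. No second operator is described, so the three terms most naturally name one role. The null stimulus is a worn device on which sonication is not started, and no sham mode that would hide this from the operator is described. The {11a} statement and the {17a} statement cannot both hold. The blinding of patients, assessors and analysts is not contradicted.

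**Step 2. What is randomised.** {16a}/{16b} randomise patients to groups. {11a} uses CT to locate the lesions but gives no rule for choosing between two sides or two parts, and it leaves probe position to the operator. The within-patient assignment is therefore a choice.

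**Step 3. How selection could act (illustration only).** The protocol gives no SD or correlation, so everything here except n and alpha is assumed.

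- n = 66/3 = 22 self-control patients (Sample size {14}); two-sided alpha 0.05.
- Baseline log-volume has SD 1 in each area, and a patient's two areas are independent.
- ρ is an area's baseline-to-day-7 correlation; s is day-7 SD divided by baseline SD.
- There is no true effect, and the larger area is always treated.

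The expected fall in log-volume rises with baseline at slope b = 1 − ρs. The larger of two independent standard normal values exceeds the smaller by 2/√π = 1.128 on average, and the variance of that gap is 2(1 − 2/π) = 0.727. Hence:

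- mean paired difference = 1.128·b
- variance = 0.727·b² + 2·s²(1 − ρ²)

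With s = 1:

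| ρ | mean | SD | mean/SD |
|---|---|---|---|
| 0.9 | 0.113 | √(0.0073 + 0.380) = 0.622 | 0.18 |
| 0.8 | 0.226 | √(0.0291 + 0.720) = 0.866 | 0.26 |
| 0.7 | 0.338 | √(0.0654 + 1.020) = 1.042 | 0.32 |
| 0.5 | 0.564 | √(0.182 + 1.500) = 1.297 | 0.43 |

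For scale, a paired t-test with n = 22 (noncentral t) rejects in 7%, 15%, 27% and 61% of trials when the difference is shifted by 0.1, 0.2, 0.3 and 0.5 SD.

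Simulation (20,000 trials per setting) gave these two-sided rejection rates. VAR assumes a mean fall of 1 log unit.

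| Setting | ρ = 0.9 | 0.8 | 0.7 | 0.5 |
|---|---|---|---|---|
| s = 1, log-volume change | 13% | 21% | 31% | 50% |
| s = 1, VAR | 12% | 18% | 24% | 34% |
| s = 1, half the choices follow size, log-volume change | 7% | 9% | 11% | 15% |
| s = 1/ρ (change independent of baseline), log-volume change | 5% | 5% | 5% | 5% |
| area chosen at random, log-volume change | 5% | 5% | 5% | 5% |

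Separate runs differ by about one percentage point. With s = 1.3/ρ the slope is b = 1 − 1.3 = −0.3 and the bias reverses: log-volume rejection rates are about 37% at ρ = 0.9 and 19% at ρ = 0.8, almost all against LIPUS.

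**The case against.** Several points on the other side are sound.

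- **No bias is demonstrated.** The inflated rates come from assuming equal spread at both times, which makes larger lesions shrink more. If change does not depend on baseline size, choosing by size does no harm; with more spread at day 7 it works against LIPUS. This stands. The figures show only that the result can depend on the choice.
- **Scale.** The endpoint is AAR or VAR, not log-volume change, and the rates on VAR are lower. This stands, and both are shown.
- **Blinded readers and analysts.** These are already planned. They guard against biased measurement and analysis. They do not guard against a biased choice of which area is treated.
- **Wording.** {16c} says the code is given before intervention; it does not mention probe placement. That the operator, experimenter and treating clinician are one role is the natural reading, not an explicit statement.
- **Condensed article.** The full protocol may hold an area rule. But the article reports its randomisation and describes patients only, and the blinding contradiction is on the page in any case.

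A reader might infer that the LIPUS-versus-control comparison is compromised too, because an unblinded operator places the probes. The article does not support that. Nowhere does it say that probe placement defines the target site for AAR and VAR, or that operators select among lesions in those two groups. A reader might also infer that the double-blind label is wholly false. It is not, since patients and assessors are stated to be blind.

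**Conclusion.** The point holds in two parts. The statement that operators are unaware of the grouping is contradicted by two other sections; this rests on the text alone, with the three role names read as one. Separately, the treated area in the self-control group is assigned by no stated rule, so a contrast that is part of the primary outcome is not protected against selection by an operator who knows the allocation.

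What is shown is a risk. Its size and direction cannot be obtained from the article. The illustration runs from no inflation, through rates several times the nominal 5%, to a bias against LIPUS, depending on assumptions about lesion behaviour that the article does not supply. Analysis cannot restore a missing random assignment afterwards, so the matter has to be settled before areas are treated.

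**What to change.** 1. For self-control patients, mark both candidate areas on the baseline CT before the envelope is opened, and put a random left/right or upper/lower assignment in that same envelope.
2. State that the blinded CT reader measures both marked areas without knowing which was sonicated, with the link to treatment made only in the database.
3. Reconcile Trial design {8} and Intervention description {11a} with {16c} and {17a}: participants, assessors and analysts are blinded, the operator is not, and the operator takes no part in outcome assessment.
4. For any self-control patient treated before this change, report how the area was chosen and describe that contrast as non-randomised.

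The cost is one extra column in the randomisation list, the marking of a CT that is already taken, and corrected wording. No extra visits, scans or staff are needed.

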Overactivated inflammatory response and abnormal immunologic state in patients with viral pneumonia were significantly associated with a high risk of severe cases [12, 13]. Given that LIPUS can up-regulate the expression of anti-inflammatory genes, upregulate immunosuppressive cell regulators and anti-inflammatory cytokines [14], and play a good role in mitigating inflammation, we tried to use wearable LIPUS to irradiate lung inflammation to improve clinical symptoms and shorten the disease course. At the same time, the physical effect of LIPUS can promote the loosening of the sputum scab attached to the inner wall of the small bronchi through low-frequency impact force [15, 16] and promote the discharge of sputum in the small airway. The mechanical and cavitation effect of ultrasound can also destroy the thrombus surface, expose the thrombolytic site, and promote the combination of thrombolytic drugs with fibrin to promote thrombolysis [17], thereby improving pulmonary blood circulation and preventing venous stasis.

Therefore, we propose a strategy of LIPUS treatment program for patients with viral pneumonia. We aim to conduct a randomized double-blind controlled clinical superiority trial that could evaluate the efficacy of LIPUS on hospitalized patients with viral pneumonia.

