#### Secondary objectives

To determine whether there is a difference in pulmonary function between LIPUS treatment group and control groupTo determine whether there is a difference in arterial oxygen saturation and serum inflammatory factor levels between LIPUS treatment group and control groupTo determine whether there is a difference in the improvement of clinical symptoms among patients

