## Outcomes {12}

### Primary outcome

The primary outcome measure will be the difference in the extent of absorption and dissipation of lung inflammation on CT images. Result comparisons will be made between the test group and the control group and between the LIPUS-treated and non-treated areas within the self-control group.

Pulmonary inflammation on CT images will be assessed by an expert chest radiologist before and 7 days after treatment to compare the area and volume of inflammation in the target area of the lung, as well as the area absorption rate (AAR) or volume absorption rate (VAR). A Pair software will be used to mark and 3D reconstruct the target area of CT images and record the data of pulmonary inflammation changes. AAR is defined as [(target site inflammation area before treatment − target site inflammation area after treatment)/target site inflammation area before treatment] × 100 (%). VAR is defined as [(target site inflammation volume before treatment − target site inflammation volume after treatment)/target site inflammation volume before treatment] × 100 (%).

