#### Serum inflammatory factor levels

Before and 7 days after treatment, nurses will draw 5 ml of fasting venous blood from patients in the morning and detect the proportion of inflammatory cells and the levels of inflammatory factors such as C-reactive protein (CRP), tumor necrosis factor (TNF)-α, interleukin (IL)-1, IL-2, IL-6, and IL-8, and procalcitonin (PCT) in peripheral blood.

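### The untreated area in the self-control arm is assumed unaffected on beam geometry alone; if any benefit carries over, this primary contrast measures only the local excess effect, and the Discussion's decision rule would misread a null

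*Protocol article*

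**What the plan says.** The Primary outcome section of the protocol article names two comparisons on CT. One is the test group against the control group. The other is "between the LIPUS-treated and non-treated areas within the self-control group".

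The Intervention description {11a} explains why the untreated area may serve as a control. In bilateral disease one lung is treated and the other is the control, because "ultrasound cannot penetrate through one lung tissue to the other, and its maximum penetration depth is limited to the inside of the target lung". In unilateral disease the inflamed area is split into an upper and a lower part and one part is treated. The argument there is beam width and plane of sonication, and the conclusion is that "the non-target inflammatory area above or below can be considered not to be affected". The same section says that the beam direction can be set by hand.

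Other sections describe how LIPUS is expected to work and what will be measured:

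- Background and rationale {6a} says that LIPUS can "upregulate immunosuppressive cell regulators and anti-inflammatory cytokines". It also gives local mechanical effects, for example that LIPUS can "promote the loosening of the sputum scab attached to the inner wall of the small bronchi through low-frequency impact force".
- The Secondary objectives include looking for a "difference in arterial oxygen saturation and serum inflammatory factor levels between LIPUS treatment group" and the control group. The section on serum inflammatory factor levels lists, among others, "interleukin (IL)-1, IL-2, IL-6, and IL-8, and procalcitonin (PCT) in peripheral blood".
- The Discussion fixes how the results will be read. LIPUS better than both comparators means effective. Better than control but not different from self-control means a fair effect that may reflect individual differences and needs a larger sample. Different from neither means poor.

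**The concern.** A within-patient control works only if treating one area leaves the other untouched. The protocol rules out direct sonication of the other area but gives no argument against a biological effect there. Cytokines and immune regulators are not confined to a sound beam, and the trial considers a change in peripheral blood plausible enough to test. In unilateral disease the control is the adjoining part of the same inflamed area, so separation is weakest there.

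If some benefit does carry over, two things follow. The within-patient contrast no longer estimates the effect of LIPUS against no LIPUS, only the excess in the sonicated area. And the Discussion's middle category would attach the wrong explanation to the result: a real benefit shared by treated and untreated lung could give exactly the pattern of better than control with no within-patient difference, which the Discussion attributes to differences between patients. No planned comparison described in the article would help to separate the two explanations.

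**Working it through.** **Inputs.** Sample size {14} gives two-sided α = 0.05, 90% power and 66 participants at 1:1:1, so 66 / 3 = 22 per arm. It gives no effect size, no standard deviation and no paired standard deviation. The carry-over fraction s appears nowhere; I assume a range of 0 to 75%.

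**The plan's own figure.** Inflation for dropout: 66 / (1 − 0.05) = 69.5, rounded up to 70, as stated. The base of 66 cannot be reproduced without an effect size. The rest is therefore anchored on the stated 90% power and is an illustration, not a check of the sample size.

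**Effect implied by 90% power at 22.** z(0.975) + z(0.90) = 1.960 + 1.2816 = 3.2415.

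- Paired standardised difference: 3.2415 / √22 = 0.69 (0.725 with the noncentral t distribution).
- Between-arm standardised difference: 3.2415 × √(2/22) = 0.98.

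**Attenuation.** Let the treated area gain Δ from LIPUS and the untreated area gain sΔ. The within-patient contrast is Δ − sΔ = (1 − s)Δ. Hence

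- power = Φ[(1 − s) × 3.2415 − 1.960]
- pairs needed for 90% = 22 / (1 − s)², rounded up

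| s (assumed) | argument of Φ | power | pairs for 90% |
|---|---|---|---|
| 0 | 1.282 | 90% | 22 |
| 10% | 0.957 | 83% | 28 |
| 25% | 0.471 | 68% | 40 |
| 50% | −0.339 | 37% | 88 |
| 75% | −1.150 | 12.5% | 352 |

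The noncentral t gives the same powers to the nearest point (13% at s = 75%). Because the scale is anchored at 90%, the power column does not depend on whether 22 pairs or the 20 implied by the Abstract's sixty participants are used.

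**LIPUS versus null stimulus.** No patient in the null-stimulus arm receives sonication, so nothing can carry over. This contrast keeps the full Δ at any s.

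**How well carry-over could be checked.** Compare untreated areas in the self-control arm with target areas in the null-stimulus arm, 22 against 22. The expected difference is sΔ. If Δ is the 0.98 SD above, power = Φ[s × 3.2415 − 1.960], which is 12.5%, 37% and 68% at s = 25%, 50% and 75%. The 95% confidence interval would extend about 2.018 × √(2/22) = 0.61 SD either side of the estimate.

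**The case against.** The best case for the plan is that the mechanism is at least partly local. Loosening sputum and disrupting thrombus happen where the beam lands, and no section says that LIPUS acts on unsonicated lung. That stands: the rationale is mixed, and s could be zero. But a mixed rationale does not justify assuming zero, and the article's argument covers the beam only.

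A reader might infer more than the documents support:

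- **That the serum objective shows the untreated area must benefit.** It does not. Serum factors could fall because the treated lung resolves and releases less. Carry-over is plausible, not established, and the bias is conditional on s > 0.
- **That a null within-patient result would be read as no efficacy.** The Discussion calls LIPUS poor only if it differs from neither comparator. With a positive result against control it says fair. The fault is the downgrade and the explanation attached to it.
- **That the trial cannot tell a whole-lung effect from no effect.** A whole-lung effect should show in LIPUS versus null stimulus, which the stated primary objective already puts first.
- **That the contrast shrinks the better LIPUS works.** At fixed s a larger Δ gives a larger contrast; only a larger s shrinks it.

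It can also be said that estimand wording and supportive comparisons are often left to an analysis plan, which is not shown. That is fair for the added comparison. It does not cover the affirmative no-effect statement or the interpretation rule, both of which are in the article.

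**Conclusion.** The point holds as a conditional one. The article justifies the untreated area as a control by beam geometry alone, while its own rationale and serum outcome make an effect beyond the beam plausible. If s > 0, the within-patient part of the primary outcome estimates only the local excess effect and is pulled towards the null by the factor (1 − s). On the illustrative scale this takes 90% power to about 68% at s = 25% and 37% at s = 50%. These figures rest on an assumed s, 22 pairs, and an effect chosen to give 90% power without carry-over. They show sensitivity and do not measure a bias in this trial.

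The LIPUS versus null-stimulus contrast is not affected. The practical harm is that the Discussion could demote a genuine positive result there to a fair effect blamed on individual differences. I read the Discussion's comparison with the self-control group as the treated-versus-untreated contrast defined under Primary outcome. If it means the LIPUS arm against the untreated areas of the self-control arm, the same attenuation applies.

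**What to change.** 1. State under Primary outcome that the treated-versus-untreated contrast within the self-control arm estimates the local effect only.
2. In the Intervention description {11a}, replace the statement that the non-target area is unaffected with the statement that it is not directly sonicated.
3. Base the efficacy conclusion on LIPUS versus null stimulus in all cases. Revise the Discussion so that a null within-patient contrast does not downgrade a positive result on that comparison, and name carry-over beside individual differences as a possible explanation.
4. Prespecify, as supportive only, an estimate with confidence interval of the difference in CT absorption between the untreated areas of the self-control arm and the target areas of the null-stimulus arm.

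The cost is wording and one extra comparison on CT data already collected. The downside lies in item 4. At about 22 per arm the estimate is imprecise, and it sets non-target areas in one arm against target areas in another. The article does not say how the treated side or part is chosen, so lesion selection could mimic or hide carry-over. The comparison must therefore not trigger a change of analysis, and a non-significant result must not be read as no carry-over. Items 1 to 3 stand whatever it shows.
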